### Qualitative Assessment

Focus groups with a minimum of 4 and a maximum of 10 participants will be performed a week after the last session; semistructured questions will be asked in order to evaluate their quality of life perception before and after the interventions. The participants invited into the focus group will be randomly chosen from a list of those who attended at least 75% of the sessions.

All the focus groups will be led by a collaborator of the research with experience conducting these sorts of groups. The content of the speeches will be fully recorded in digital audio, and then all the data will be transcribed. We expect this analysis to identify the feasibility and adherence and non-adherence to mindfulness and its health effects.

We will also apply the free evocation of words technique during the qualitative assessment. It consists of asking the interviewer to say five words (simple or compound) that come to mind when listening to the inducing terms: *body*, *aging*, *quality of life*, and *meditation*, and then it is asked to mark which of the words evoked is the most important and why. This assessment will be done on paper with the lines for the participants to write the five words and the explanation. Evocation will be organized in order of frequency and appearance. This technique is used to characterize social representation in which the frequency and orders of word evocation are calculated (82).

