Thus, the aim of this study is to evaluate the feasibility and preliminary efficacy of the MBHP program on quality of life (primary outcome) of older adults assisted in PC comparing to a cognitive stimulation active control group. Our main hypothesis is that the MBHP is feasible and efficacious in promoting quality of life in people older than 60 years, and it will improve psychological health, self-compassion level, sleep quality, religiosity, and score at ADLs and prevent or delay cognitive decline in the elderly (secondary outcomes). Also, we hypothesize that the MBHP is superior to a cognitive stimulation group to promote those benefits.

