## Materials and Methods

The “MBHP-Elderly Study” is a randomized controlled trial addressing older people with 3 assessment points (baseline, post-intervention, and 1-year follow-up) nested in a cohort study (the EPIDOSO study) of older adults patients assisted in a PC facility of the “Center for Aging Research” [Centro de Estudos do Envelhecimento (CEE)] of the Universidade Federal de São Paulo—UNIFESP.

One hundred fifty-two participants will be recruited from the cohort and then randomized into the following two experimental groups: (I) MBHP intervention group (76 participants) in which the elderly will have a weekly meeting of an hour and 30 min for 8 weeks to perform the MBI (MBHP protocol) accompanied by extra four 1-h meetings through a maintenance group with all participants after the eighth week (each maintenance session took place fortnightly), totaling a 4-month (16-week) intervention; (II) cognitive stimulation control group (76 participants) of elderly who will take computer-based cognitive stimulation classes for 4 months, once-a-week 1.5-h meetings without maintenance phase, totaling 16 weeks. In both groups, the same assessment for data collection will be applied, and they will be applied in the baseline (T0), post-intervention (T1), and 1-year follow-up (T2). Both interventions will last 16 weeks. However, the reason why the MBHP intervention group will take 12 sessions and the cognitive stimulation control group 15 sessions is because one of the aims in the MBHP intervention is to work on the participants' autonomy in their personal mindfulness practice in daily life through home activities exercises, and we wanted to compare its outcomes with the 4-month weekly meetings of control intervention, which require face-to-face sessions. Study design and participant flow through the trial is shown in Figure 1.

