### Sample Size and Power Calculations

The minimum sample for each group was identified as 64 participants to detect a power of 0.80 and an α of 0.05. These calculations were performed using the G^*^Power 3.1 software for comparison between two intervention groups with respect to the mean differences of the scores at each time point of assessment relative to baseline. Therefore, 152 individuals should be randomized to receive one of the interventions (76 in the intervention group, 76 in the control group) assuming a maximum loss of 15%.

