#### MoCA

This neuropsychological test assesses the cognitive function. It is a 12-item test that measures eight cognitive domains: short-term memory (delayed drawing), visuospatial abilities (cube drawing, clock drawing), executive function (trail-making test, phonemic verbal fluency, verbal abstraction), attention, concentration, working memory, language, and orientation to time. The test total score is 30 points where a score ≤26 indicates normality, and less indicates mild cognitive impairment (63, 64).

At the post-intervention, the feasibility and adherence of MBHP program among the participants will be assessed through a questionnaire created by our research group in order to evaluate the type, frequency, and length of personal meditative practice at home during the week out of the meetings, addressing potential unwanted effects as well. The frequency of the attendance to the weekly meeting will also be monitored. The dropout cases will be monitored, and we will make phone calls to them to ask the reasons why they were absent or did not go on attending the meetings. For more information about the target of each scale assessment and its time points, see Table 2 and Figure 2 to see each step of the study.

**Table 2 T2:** Overview of measures and time points (according to 2013 SPIRIT figure guidelines).

**Measure**	**Target**	**T0**	**T1**	**T2**
		**Baseline**	**Post-intervention**	**Follow up**
WHOQOL-BREF	Quality of life	X	X	X
WHOQOL-OLD	Quality of life of elderly	X	X	X
MoCA	Cognitive function	X	X	X
CDR	Dementia	X		
ADL	Activities of daily living	X	X	X
MAAS	Mindfulness trait	X	X	X
SCS	Self-compassion	X	X	X
PSQI	Sleep quality	X	X	X
DUREL	Religiosity	X	X	X
DASS-21	Psychological health	X	X	X

*ADL, Activities of Daily Living Scale; CDR, Clinical Dementia Ratings; DASS-21, Depression Anxiety Stress Asessment-21; DUREL, Duke Religious Index; MAAS, Mindful Attention Awareness Assessment; MoCA, Montreal Cognitive Assessment; PSQI, Pittsburgh Sleep Quality Index; SCS, Self-Compassion Scale; WHOQOL-BREF, World Health Organization Quality of Life–BREF; WHOQOL-OLD, World Health Organization Quality of Life–OLD*.

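### Focus groups drawn only from people with at least 75% attendance can inform home practice and quality-of-life perception, but not the low attendance and dropout that their analysis is also expected to explain

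*Protocol article*

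**What the plan says.** The Introduction makes feasibility a headline aim: "the aim of this study is to evaluate the feasibility and preliminary efficacy of the MBHP program".

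The Qualitative Assessment section sets the sampling rule for the focus groups: "The participants invited into the focus group will be randomly chosen from a list of those who attended at least 75% of the sessions". It gives the groups two purposes. The questions concern quality of life: "semistructured questions will be asked in order to evaluate their quality of life perception before and after the interventions". The analysis is also meant to speak to uptake: "We expect this analysis to identify the feasibility and adherence and non-adherence to mindfulness and its health effects".

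Other sources on adherence appear in the paragraph that closes the MoCA subsection of the secondary outcomes. There, "the feasibility and adherence of MBHP program among the participants will be assessed through a questionnaire created by our research group". That questionnaire covers home practice and unwanted effects. Attendance at the weekly meetings is monitored, and for dropouts "we will make phone calls to them to ask the reasons why they were absent or did not go on attending the meetings".

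The Qualitative Analyses section applies content analysis to the focus groups and to the justifications from the word-evocation task. It does not mention the telephone calls.

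**The concern.** The sampling list selects on adherence, and the analysis is then expected to identify non-adherence. Random choice within the list does not remove that selection, because everyone below the cut-off has zero probability of being invited.

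What is at stake is the qualitative part of the feasibility conclusion. The Discussion counts the focus groups among the data that should show whether the programme is feasible in primary care, and it looks ahead to use as public policy. Views on feasibility taken only from people who came to most sessions will tend to be favourable. Barriers strong enough to keep people away will be seen little or not at all in this strand.

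**Working it through.** The plan gives no figure to reproduce here. The check is a count of sessions, followed by a comparison of what each source can observe.

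**Attendance threshold.** The Materials and Methods section states that "the MBHP intervention group will take 12 sessions and the cognitive stimulation control group 15 sessions". The minimum attendance is 0.75 × sessions, rounded up.

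- MBHP: 0.75 × 12 = 9, so at most 3 missed.
- Control: 0.75 × 15 = 11.25, rounded up to 12, so at most 3 missed. The Cognitive Stimulation Protocol section describes weekly classes for 16 weeks; with 16 sessions the cut-off is also 12, with at most 4 missed.
- If only the 8 core MBHP sessions were counted: 0.75 × 8 = 6, so at most 2 missed.

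**What each planned source can show.**

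| Topic | Focus groups (at least 75% attendance) | Other planned sources |
|---|---|---|
| Quality-of-life perception before and after | Yes, among regular attenders | WHOQOL scales |
| Weak home practice despite attending | Yes | Home-practice questionnaire |
| Unwanted effects and negative views | Yes, among regular attenders | Unwanted-effects questionnaire |
| Reasons for dropping out | No, unless the person had already reached 75% | Calls to dropouts; no qualitative analysis stated |
| Reasons for low attendance while still enrolled | No | Attendance is counted; the calls are directed at dropout cases, so coverage is unclear |

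The last two rows are the gap. The fourth is filled in part and the fifth is not clearly filled.

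**How many people might be outside the list.** The article gives no attendance rate, so this is illustration only. The Sample Size section randomizes 76 per arm, "assuming a maximum loss of 15" per cent. Assume that everyone lost falls below 75% attendance, and that a further share *a* of those retained also does:

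share outside = 1 − 0.85 × (1 − *a*)

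- *a* = 0: 0.15, or 0.15 × 76 = 11.4 people.
- *a* = 0.10: 1 − 0.85 × 0.90 = 0.235, or 17.9 people.
- *a* = 0.40: 1 − 0.85 × 0.60 = 0.49, or 37.2 people.

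Both assumptions are outside the documents. The 15% is an allowance for lost assessments, not a rate of poor attendance: someone lost only at the 1-year follow-up may have attended every session. So even 15% is not a floor.

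**The case against.** The strongest reply is that the trial does ask the people concerned. Dropouts are telephoned for their reasons, attendance is recorded, and the questionnaire covers home practice and unwanted effects with no attendance threshold stated. The Abstract names adherence and unwanted-effects questionnaires as the means of assessing feasibility, so the focus groups are one contributor and not its sole basis. This stands. A reader might infer that reasons for poor attendance, or all negative experiences, are excluded from the study by design. The documents do not support that.

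Second, the stated target is non-adherence to mindfulness, not only to sessions. The programme relies heavily on home practice, and a person who came to 9 or more sessions may have practised little and can say why. Regular attenders can also report bad experiences. This stands too, so it would be wrong to say that the focus groups can tell nothing about non-adherence or feasibility.

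Third, the list suits the other stated purpose: comparing quality of life before and after requires people who received the intervention. That is a good reason to have such a list. It does not make it a sufficient list for the second purpose.

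What the reply does not remove is narrower. The article attributes the identification of non-adherence to the focus-group analysis. It states no qualitative analysis of the calls and does not link them to the focus groups.

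**Conclusion.** The concern holds for the focus-group strand, and it is minor. The sampling rule and one of the stated purposes do not fit each other: the groups can inform quality-of-life perception and non-adherence to home practice among regular attenders, but not low attendance or dropout. Their picture of feasibility will lean favourable. Other planned data partly cover the gap for the trial as a whole.

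The session counts follow from the article. The number of people outside the list cannot be established from it, and the shares worked out above should not be read as an estimate. The expected favourable lean is a judgement about who stays away, not a measured bias. The primary outcome, the sample size and the error rates are unaffected.

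**What to change.** **If the focus groups are still to be held.** Keep the present list and add a second random list of people below 75% attendance, including dropouts, with some of the 4 to 10 places per group reserved for it. Code the reasons given in the telephone calls in the same content analysis, and report themes by attendance group. State whether people who remain enrolled but fall below 75% will also be called.

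**If the focus groups have already been held.** This is possible, since the Trial Status section says the study was under way. Analyse the call data alongside the transcripts, and restrict the focus-group conclusion to the experience of those who attended at least 75% of sessions.

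**Cost.** The first option needs a few more invitations, and acceptance is likely to be lower among low attenders. With few such people per group, their themes will be thin, which is why the calls should be coded as well. The second option needs coding of reasons that the plan already collects, and a narrower sentence on what the focus groups are expected to identify.

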### Qualitative Analyses

The word evocations will be organized in order and frequency of appearance with the help of the EVOC 2005 software (83). They will be analyzed by their frequency and the order of the evoked sequence, estimating their evocation mean order. The order and frequency in which the first words evoked were evoked demonstrate the most strongly associations linked to collective affections and imaginary.

The justifications content of the words obtained in the evocations, as well as in the focus groups, will be analyzed from the thematic–categorical content analysis technique, considering the analytical categories and apprehension of the empirical categories arising from the content of the speeches. The technique of content analysis aims to describe the manifest content objectively, systematically, and quantitatively with the purpose of its interpretation (84). NVivo software version 12 will be used to aid in the processing, organization, coding, and thematic analysis.

### Ethical Considerations

This study was registered under ClinicalTrials.gov as NCT03706807 retrospectively on October 11, 2018, and it was submitted to the Research Ethics Committee/Plataforma Brasil–UNIFESP and approved under CAAE 89700318.0.0000.5505 and opinion number 3.557.601. The SPIRIT statement recommendations for clinical trials were adopted (45). The participants of the research will receive a written informed consent to be signed.

### Trial Status

At the time of this manuscript submission, the recruitment for the MBHP-Elderly Study was already ongoing (started in June 2018 and predicted to finish in February 2021 with the follow-up collection).

## Discussion

By the progressive increase of the elderly population in Brazil and all over the world, it is necessary to study accessible, feasible, and efficacious interventions that promote healthy aging and improve quality of life of this population. Research on MBIs with older participants is still scarce in the literature. The MBHP-Elderly Study will assess the effects of the MBHP program on quality of life (primary outcome), cognitive function, psychological health, mindfulness, sleep quality, self-compassion, and spirituality at three assessments points (preintervention, post-intervention, and follow-up) to investigate the potential gains of the intervention and if it is maintained over time. To the best of our knowledge, the MBHP-Elderly Study is the first to propose such research question in a Latin population considering its own cultural and healthcare aspects.

Mindfulness-based interventions have been associated with quality of life in adults in several studies (14, 16, 85, 86), and a previous study has shown high levels of adherence to an MBI in Brazil (13). According to the literature, people who practice mindfulness in their lives have fewer symptoms of anxiety and depression and deal better with dysfunctional stress and chronic pain (13, 20, 21). Therefore, we believe that these interventions can have positive outcomes in improving the quality of life of the elderly assisted by the PC, and in this study, we will also monitor the level of adherence of the older adults at post-intervention and 1-year follow-up.

We hope to demonstrate, assuming our priori hypothesis is true, that health promotion effects of MBHP are also valid for the elderly population. There are a few studies that show the effect of MBIs on older adults, but controlled and randomized clinical trials are scarce (43), and especially with mixed methods. Moreover, there is not any study that evaluated MBHP protocol directed at older people yet. This will be the first study of the MBHP with older people with qualitative and quantitative method assessments. If the findings of this study confirm the effectiveness of this program in this population, it will be possible to consider it as intervention to be implemented in other health facilities and as a public policy addressed to older people.

One potential limitation of the study is the lack of a second and passive control group composed of a waiting-list participant, besides the active control group. There is a growing discussion over the use of waiting-list control group in psychological and behavioral research (87). Some researchers will argue that to evaluate the effects of interventions it is better to have three groups: an intervention, an active control group of a treatment as usual, and a passive control group that does not receive any treatment. Due to ethical issues (both mindfulness and cognitive stimulation are expected to promote positive effects based on previous studies) and the well-known difficulties to recruit a large number of older persons to research protocols, we decided to opt for two groups with a statistically sound calculated sample.

Furthermore, the fact that when multiple constructs are being measured using common methods and surveys may lead to spurious effects due to the measurement instruments rather than to the constructs being measured is well-known. For instance, false correlations are likely to be produced among the items owing to response styles or social desirability.

Despite these limitations, the present study, which uses qualitative and quantitative approaches, may bring a better understanding of how MBIs may improve the quality of life in objective and subjective perspectives within a mixed-methods approach. Psychometrics parameters and qualitative assessment through focus group and the word free evocation technique may bring a range of meaningful data to find out how mindfulness training may work on older people and if the MBHP program is feasible and efficacious when applied for older population in PC.

## Ethics Statement

The studies involving human participants were reviewed and approved by UNIFESP Research Ethics Committees under the number 2.776.081. The trial was registered on ClinicalTrials.gov under the number NCT03706807 on October 11th 2018. The patients/participants provided their written informed consent to participate in this study.
